#### Secondary outcomes

##### Physical activity

For a subset of randomly selected (stratified by sex and group) participants (*n* = 60), PA will be objectively assessed using GENEActiv wrist-worn accelerometers (Model GAT04, Activinsights Ltd, Cambridgeshire, England) over a span of four weeks, comprising one week before and after the intervention as well as the initial and concluding weeks of the intervention. Participants will be encouraged to wear the device 24 h/day, without taking off even when bathing or sleeping. GENEActive accelerometers have demonstrated acceptable reliability and validity for PA monitoring in adolescents (44). The cut-points employed to categorise sedentary, light, moderate and vigorous PA are <6, 6–21, 22–56, and >56 g s, respectively (44).

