## Methods and analysis

### Study design

The study is a multi-centre collaborative work conducted by University of Exeter and Ningbo University. Consolidated Standards of Reporting Trials (34) and Template for Intervention Description and Replication (35) checklists will be adopted for guidance and reporting. The *PRO-HIIT* study will employ a two-arm cluster-randomised controlled trial design, with an intervention group and a treat as usual control group. Clusters in this study are eight classes of secondary school students, located in Ningbo City, China. The intervention will be delivered five times per week, commencing at the beginning of the three PE and two PA lessons. The PA lessons serve as a complementary opportunity for students to engage in exercises of their choice on days when PE lessons are not scheduled. Assessments will occur at three time points: baseline (T1), immediate post-intervention (T2) and two-month post-intervention (T3), with T3 aligning with the initial two weeks of a new school term following a two-month unstructured summer holiday. Table 1 presents an overview of the schedule for recruitment, intervention delivery and outcome assessments.

**Table 1 T1:** Overview of the *PRO-HIIT* intervention.

Procedures		Recruitment & pre-intervention measurements				Intervention phase (12 weeks)												Post-intervention measurements			Summer holiday	Follow-up measurements	
	22–26 Jan	26 Feb–22 Mar				25 Mar–14 Jun												17–28 Jun		1–4 Jul	5 Jul–1 Sep	2–13 Sep	
	2023–2024 school term 1	2023–2024 school term 2																				2024–2025 school term 1	
	week 22	week 1	week 2	week 3	week 4	week 5	week 6	week 7	week 8	week 9	week 10	week 11	week 12	week 13	week 14	week 15	week 16	week 17	week 18	week 19		week 1	week 2
Eligibility screening		√																					
Consents & assents																							
Training workshop			√																				
Randomisation					√																		
Maturity				√																			
PA (GENEActiv)					√	√											√	√					
PA (questionnaire)				√														√				√	
Sleep																							
Body composition																							
CRF																							
Muscular strength																							
Bone health																							
Executive function																							
Wellbeing																							
Enjoyment																							
Motivation																							
Affect																							
Self-efficacy																							
Academic assessment	√																			√			

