### Recruitment and allocation

An invitation letter will be sent to nearby secondary schools at Ningbo University. When schools express their interest, contacts will be initiated to elucidate the participation requirements. Upon agreement from the schools, invitations will be extended to head teachers and PE teachers of year 7, who will then present the study to students for recruitment. To be eligible for participation, students are required to submit signed assent forms along with signed consent forms from their parents/guardians. Students with health or medical conditions that would restrict their ability to engage in vigorous PA will be excluded from the study. The screening process will involve reviewing the medical examination reports submitted by the participants’ parents or guardians. Classes will be randomly allocated to either *PRO-HIIT* group or control group, via a computer-based random number generator by an independent researcher. The randomisation and allocation will take place after baseline assessment. The randomisation will be stratified by PE teacher, wherein each teacher's classes will be randomly assigned to either the intervention or control group.

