### Intervention delivery and exercise design

The present study is a quality PE/PA intervention in which a resistance-based HIIT session is embedded in the first 6–10 min of regular PE and PA lessons, replacing traditional warm-up activities. The intervention will be delivered five times a week—three PE and two PA lessons—over twelve weeks (from school term 2, week 5 to week 16, March to June 2024). Throughout the intervention, PE teachers will coordinate and supervise the HIIT intervention, while the delivery will be accomplished by two student peer-coaches, selected by the PE teacher within each intervention class. The control group will maintain their traditional warm-up activities, such as light running and static stretching.

To ensure quality and effective implementation, the leading researcher will collaborate with the PE teachers and peer-coaches for delivering the intervention during the initial two weeks. Researchers will visit the school once per month to provide on-going support and guidance. Additionally, a training logbook at each intervention class will be maintained by the PE teachers to document aspects, such as attendance, dose delivered and received, and adverse events. These records will be sent to researchers on a weekly basis to ensure prompt feedback and communication. In cases where HIIT sessions are cancelled due to inevitable factors such as large school events or severe weather, participants will be encouraged to complete these sessions during alternative times (e.g., breaks). These additional sessions will be supervised by peer-coaches and will be recorded in the training logbook. The control group will take their regular PE and PA lessons as usual.

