### Outcome measurements

Outcome measurements will be conducted in the school premises by trained research assistants who will remain blinded to group allocation throughout all assessment time-points. All measurements will be introduced and explained during the training workshop and will be described again prior to the commencement of the measurements to ensure clarity. The measurements will be conducted during their regular PE lessons. Details of the outcome measures are summarised in Table 5.

**Table 5 T5:** How, when and where the outcome variables will be measured.

Outcomes	Tools	Timing	How and where (all participants, measured at class level)
Physical activity	GENEActiv	One week before and after intervention, first and last week of intervention.	A subsample of 60 participants (30 in each group, 30 males) will be randomly selected to wear the GENEActive accelerometer for 14 days consecutively for twice, covering the total 4 weeks.
Cardiorespiratory fitness	20 m shuttle run	T1, T2, T3	Multiple measurement stations will be held, and participants will be split into groups to ensure efficient measurements. Two physical education lessons are estimated to be sufficient. All these measurements will be conducted in sports hall.
Body composition	TANITA	T1, T2, T3	
Muscular strength	Handgrip, standing long jump	T1, T2, T3	
Bone health	GE Achilles	T1, T2, T3	
Executive function	Flanker tasks, visual 2-back tasks, colour-shape switch tasks	T1, T2, T3	Perform the executive function tasks online in a school computer room in one physical education lesson (40 min).
Wellbeing	SDQ	T1, T2, T3	Finish together using one physical education lesson (40 min) in a school computer room with the instruction of research staff.
Enjoyment	PACES	T1, T2, T3	
Motivation	BREQ-2	T1, T2, T3	
Affect	PANAS-SF	T1, T2, T3	
Self-efficacy	PPAS	T1, T2, T3	
Academic performance	End-of-term academic examinations	By the end of term 1 and T2	Obtained directly from head teacher.

SDQ, strength and difficulty questionnaire; PACES, physical activity enjoyment scale; BREQ-2, exercise regulations questionnaire; PANAS-SF, positive and negative affect schedule short form; PPAS, perceived physical ability scale; T1, pre-intervention; T2, immediately post-intervention; T3, 2-month follow-up.

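### Drawing the accelerometer subset by trial arm puts its only pre-intervention week after allocation, against the protocol's rule that randomisation follows baseline

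*Protocol article*

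**What the plan says.** Four parts of the protocol article bear on this.

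- **Secondary outcomes, Physical activity.** The accelerometer sample is described as "For a subset of randomly selected (stratified by sex and group) participants", with n = 60.
- **Outcome measurements, Table 5.** "A subsample of 60 participants (30 in each group, 30 males) will be randomly selected to wear the GENEActive accelerometer". The device is worn in two runs of 14 consecutive days, timed as "One week before and after intervention, first and last week of intervention".
- **Recruitment and allocation.** Classes are the unit allocated, by an independent researcher and stratified by PE teacher. On the order of events: "The randomisation and allocation will take place after baseline assessment".
- **Study design, Table 1.** By column position, randomisation is ticked in week 4 of term 2 and GENEActiv wear in weeks 4, 5, 16 and 17. Week 4 stands under the pre-intervention measurement heading. The intervention section dates delivery "from school term 2, week 5 to week 16, March to June 2024".

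**The concern.** An arm exists only once classes have been randomised. A draw stratified by arm therefore comes after randomisation, and the device can be fitted only after the draw. For this outcome the pre-intervention reading then follows allocation, and the recruitment section makes no exception for it.

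The planned model is a linear mixed model with group, time and their interaction. Week 4 is the only reading that can serve as the pre-intervention time point. If pupils know their arm by then, two things could happen: behaviour in the baseline week could respond to that knowledge, and agreement to wear the device could differ by arm. This is the trial's only device-based activity measure. The other, the IPAQ-SF, is self-reported and is listed as a confounder.

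**Working it through.** **Calendar.** Table 1 starts week 1 on 26 February (2024) and gives 26 February to 22 March for weeks 1 to 4.

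| Week | School days | Table 1 |
|---|---|---|
| 3 | 11–15 March | maturity, activity questionnaire |
| 4 | 18–22 March | randomisation; GENEActiv |
| 5 | 25–29 March | GENEActiv; HIIT begins |
| 16 | 10–14 June | GENEActiv; last HIIT week |
| 17 | 17–21 June | GENEActiv |

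The plan's own figure reproduces: 2 runs × 14 days = 28 days = 4 weeks, namely 18–31 March and 10–23 June.

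**Order of events.** A full week of wear before 25 March has to begin on 18 March. Drawing by arm requires allocation before the devices go on, so by about 18 March. If allocation came at the end of week 4 instead, a draw by arm could not supply a full pre-intervention week. The draw by arm, the full week before and the rule that randomisation follows baseline therefore cannot all hold for this outcome.

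**How a week-4 difference would act.** For a later week w, the change contrast is

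(intervention mean at w − intervention mean at 4) − (control mean at w − control mean at 4).

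If allocation shifts the intervention mean in week 4 by δ, the contrast moves by −δ. A comparison of the two arms at week w alone contains no week-4 term, so a week-4 response does not enter it.

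**Scale.** With 30 per arm and no clustering, the standard error of a difference in mean change is √(2/30) = 0.258 SD of change. The protocol gives no value for δ. For illustration only, an assumed δ of 0.1 to 0.2 SD of change is 0.1/0.258 = 39% to 0.2/0.258 = 78% of that standard error. Clustering by class would raise the standard error and lower these percentages.

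**Can the subset be drawn without using the arm?** The focus-group section invites four pupils from each intervention class, 16 in all, so there are 16/4 = 4 intervention classes and 8 − 4 = 4 control classes.

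- 60/8 = 7.5 pupils per class, so four classes give 7 and four give 8: 28 + 32 = 60.
- At worst all four classes of 7 fall in one arm, giving 28 against 32.
- Suppose each of four PE teachers has two classes, one going to each arm (the number of teachers is not given). Taking 7 per class for two teachers and 8 per class for the other two gives 7 + 7 + 8 + 8 = 30 per arm exactly.
- Thirty boys remain feasible: 4 boys in each class of 8 (16), and 3, 3, 4 and 4 in the classes of 7 (14).

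**The case against.** **The accelerometer week may lie outside baseline.** Table 5 marks most outcomes T1, T2 and T3 but gives the device its own timing, so the order rule could be read as covering T1 only. This softens the conflict without removing it: Table 1 files week 4 under pre-intervention measurements, and it is the only pre-intervention device reading.

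**Generating allocation is not disclosing it.** Only the person drawing the sample needs to know the arms, and an independent researcher runs the randomisation. The protocol does not say when classes are told. This stands. The order conflict follows from the text, but bias needs disclosure before or during the week-4 wear, which is not stated.

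**Thirty per arm can be reached without knowing the arms.** True under the teacher arrangement shown above. But the text stratifies by group, which is a different procedure.

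A reader might also infer stronger points that the document does not support:

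- *That intervention pupils practise HIIT in the baseline week.* Table 1 ticks the training workshop in week 2. The executive function section does place a workshop one week before the intervention, but describes only practice of the cognitive tasks.
- *That the activity outcome loses randomisation altogether.* A random draw within randomised arms remains comparable, and comparisons within weeks 5, 16 and 17 do not use week 4.
- *That baseline generally follows allocation.* Maturity and the activity questionnaire are ticked in week 3. The ticks for fitness and the other measures are not legible in the text at hand, so nothing follows for them.
- *That the sample ignores class.* The article is silent on this, and such detail may sit in the full protocol.

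**Conclusion.** The inconsistency is real and limited. As written, the accelerometer subset can be drawn only once the arms are known, so its pre-intervention reading follows allocation, contrary to the stated order. The order within week 4 is inferred from the draw by group and the need for a full week of wear before the intervention; the protocol does not spell it out.

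Whether bias results depends on allocation being disclosed before or during that wear, and its size is unknown. The illustrative 0.1 to 0.2 SD has no source in the protocol. The exposed analyses are the group × time contrasts that use week 4, for one secondary outcome in 60 pupils. The primary outcome is not affected. Comparisons within weeks 5, 16 and 17 are free of any week-4 response. They do assume that agreement to wear the device did not depend on the arm, since that would change who is in the sample. The point deserves correction because the remedy is cheap.

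**What to change.** 1. In the physical activity section and Table 5, replace sampling by group with: *stratified by sex and class, drawn before randomisation, 7 or 8 pupils per class*. Balance the sevens and eights within PE-teacher strata where possible.
2. Fit the devices before allocation is generated. Failing that, have the independent researcher withhold allocation from classes, pupils and teachers for as much of the week-4 wear as the arm-specific workshops allow. State the disclosure date.
3. Treat only wear days before disclosure as baseline. Disclosure on Wednesday 20 March would leave two full days (18–19 March); Friday 22 March would leave four (18–21 March).
4. Reconcile the workshop dates with this order. Table 2 makes the pupil workshops arm-specific, yet Table 1 puts the workshop in week 2, before randomisation, and the executive function section puts one a week before the intervention.
5. If the subset has already been drawn by arm, state this as an exception to the order rule and report how many pupils were approached and agreed in each arm.

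**Cost.** The devices and calendar weeks are unchanged. The split may be as uneven as 28 to 32, and there are fewer baseline days. This is more than a wording change: holding allocation until Friday 22 March leaves no school day for the arm-specific workshops before HIIT starts on Monday 25 March, and the weekend of 23–24 March would still be worn after disclosure. An earlier disclosure buys workshop time at the price of baseline days.

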##### Body composition

Height and waist circumference will be measured with a portable stadiometer and a tape, respectively. Subsequently, waist-to-height ratio will be calculated (45). Body mass and body fat percentage will be determined with a Tanita device (Tanita Corp., Tokyo, Japan).

##### Muscular strength

Upper and lower body strength will be assessed using hand grip and standing long jump, respectively. A digital dynamometer with an adjustable grip, with participants standing and elbow in 90-degree flexion, will be employed for measuring the upper body strength in kilogrammes (46). The test will be performed once on both hands and the highest record will be reported. Standing long jump will be measured with a standing long jump mat. Participants stand behind the start line with their feet apart and are allowed to swing their arms quickly to jump as far as possible. Each participant will have three attempts, with the best one recorded.

##### Bone health

A heel ultrasound test will be performed via a GE Achilles heel ultrasound machine (GE Medical Systems Lunar, USA). Participants will be seated with one foot on the foot plate, and alcohol will be applied to ensure proper membrane contact. A transducer on one side of the heel will convert an electrical signal into a sound wave, which will pass through the heel to the other side and be received and analysed by another transducer. The speed of sound (SOS, in m/s) and broadband ultrasound attenuation (BUA, in dB/MHz) will be measured and used to calculate the stiffness index (SI) with the equation: SI = (0.67 × BUA + 0.28 × SOS) − 420 (47). The test will be performed on both feet and an average score will be recorded.

##### Executive function

Participants’ executive function will be assessed on aspects of inhibition, working memory, and cognitive flexibility (48). Three tasks will be utilised, including flanker task, visual 2-back task and colour-shape switch task. The tasks are adapted from studies conducted by Wassenaar and colleague (49) and will be programmed on the Gorilla platform (50). The order of the three tasks will be randomised at individual level and will be performed collectively within the school computer room on a class-unit basis, with the presence of researchers to provide clarification if needed. One week prior to the intervention, a training workshop will be conducted to acquaint participants with the executive function tasks. A ten-minute presentation will elucidate the task procedures by research staff, and participants will engage in hands-on practise for each task. Any questions and inquiries will be addressed within the workshop to ensure clarity and understanding. Details for the three tasks are provided in the Additional File S1.

##### Wellbeing

The Chinese version of the Strengths and Difficulties Questionnaire (SDQ) will be used to assess the psychological distress of participants (51). The questionnaire will be administered online via the Gorilla platform following the completion of executive function tasks. The SDQ comprises 25 personality items, rated on a 3-point scale (i.e., “*not true”* *=* *0, “somewhat true”* *=* *1* and “*certainly true”* *=* *2*), and is composed of five subscales, each consisting of 5 items. These subscales include emotional symptoms, conduct problems, hyperactivity/inattention, peer relationship problems and prosocial behaviour. The total difficulties score ranges from 0 to 40, where a score ≥ 17 is considered as high difficulties (52).

##### Enjoyment

Enjoyment of PA will be measured using the Physical Activity Enjoyment Scale (PACES) (53), which is validated among adolescents (54). The scale commences with a prompt “when I am active” followed by 16 phrases that participants will rank on a 5-point scale, ranging from 1 (Disagree a lot) to 5 (Agree a lot). The enjoyment score ranges from 16 to 80, with a higher score representing higher level of PA enjoyment (54).

##### Motivation

Motivation to autonomously engage in PA will be assessed using a modified Behaviour Regulation in Exercise Questionnaire (BREQ-2), which is an 19-item validated questionnaire (55). The scale comprised of 5 subscales, including intrinsic, identified, introjected, external and amotivation. Each item was rated on a 5-point Likert scale ranging from 0 (“not true for me”) to 4 (“very true for me”). The mean of the 5 subscales will be calculated to reflect the extent of each motivation type separately. A Relative Autonomy Index will be adopted by weighting (intrinsic * 3, identified * 2, introjected * −1, external * −2 and amotivation * −3) the subscales and summing the weighted scores (56). The Relative Autonomy Index ranges from −24 to 20 and higher positive scores indicate more autonomous motivation.

##### Affect

Affect will be assessed via a Chinese version of the International Positive and Negative Affect Schedule Short Form (PANAS-SF) (57). This 9-item questionnaire utilises a 5-point Likert scale, ranging from 1 (Not at all) to 5 (Extremely). Comprising 5 items related to positive affect and 4 items pertaining to negative affect, this instrument is considered reliable for its implementation in Chinese adolescents (57). The positive and negative affect scores will be summed and reported separately, with higher positive score indicates more positive affect and lower negative score indicates less negative affect.

##### Self-efficacy

A 6-item validated Perceived Physical Ability Scale (PPAS) will be utilised to evaluate the PA-related self-efficacy (58). In each item, four statements related to capabilities for doing exercises will be given and participants will be required to choose the one that best representing their personal feelings. The total score ranges from 1 to 24, with higher scores indicate a higher self-perception of physical ability and vice versa.

##### Enjoyment and satisfaction

Enjoyment and satisfaction of the HIIT workout will be evaluated using a 2-item 5-point Likert scale, with the prompt: “I enjoyed/liked the HIIT workouts” and “I will continue to perform/use the HIIT workouts” between 1 = strongly disagree and 5 = strongly agree. This will only be assessed post-intervention among participants in the intervention group (T2).

##### Academic performance

Academic performance will be evaluated by utilising the school's end-of-term academic examinations, which comprehensively assess all the subjects. Mathematics, language learning (main subjects in Chinese secondary school) and a composite score for all subjects will be utilised to discern variations in academic performance between the intervention and control groups. Therefore, academic performance will not be assessed at the follow-up stage.

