### Sample size estimation

A sample size estimation was calculated based on CRF using the 20 m shuttle run test (20 m-SRT). Previous studies reported 9 laps of improvement, with effect size of *d* = 0.31 (36) and *d* = 0.69 (37), achieved through 12 or 14 weeks of resistance-based HIIT, respectively. In the current study, a conservative effect size of *d* = 0.31 was utilised for power calculation. Therefore, based on a G*Power (Version 3.1) calculation (38) and using two groups with 80% power at an α of 0.05, it is estimated to recruit 165 participants in each group. With an average enrolment of 50 students in secondary school classes in Ningbo and a conservative 20% of dropout rate (39), it is deemed that 8 classes (approximately 50 participants per class) would provide sufficient statistical power for analysis. Given the typical scale of a Chinese secondary school (10–15 classes per grade), the 8 classes will be recruited from one secondary school.

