#### Statistical analyses

Data entry will be completed by one researcher with a random sample of at least 10% of entries cross-checked by a second researcher for accuracy. Prior to analysis, thorough checks for outliers and errors will be conducted using range and boxplot methods. Additionally, assessments for normality, homogeneity of variances and sphericity will be conducted as needed to verify assumptions. The baseline data for intervention and control groups will be presented and compared at individual level using independent sample *t*-test. An intention-to-treat approach will be adopted to evaluate the effects on outcome variables to avoid bias in exploring the impact of the intervention. Linear mixed-effect models will be used, with random effects, to analyse the impact of groups (intervention and control), timepoints (pre-, post-intervention and follow-up) and group × time interactions. Statistical analyses will be adjusted for the clustering effects at class level. Per protocol sensitivity analysis will be undertaken at the class level. Considering for disruptions such as school holidays, exams, severe weather, a minimum of 30 sessions is considered achievable over the 12-week period. Other sensitivity analyses, such as complete-case analysis, will be conducted where appropriate. Moderators, including sex (male, female), baseline overweight/obese (yes, no) and baseline CRF (healthy vs. needs to improve), will be examined with linear mixed models. Where appropriate, subgroup analyses will be conducted for the significant group-by-moderator interactions. PA, sleep and maturity will be included in the model to eliminate confounding effects. All data analyses will be conducted via IBM SPSS Statistics for Windows (SPSS 28.0; IBM Corporation, Armonk, NY, USA), with an alpha level of 0.05.

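### Academic performance comes from two different end-of-term examinations, and the general three-timepoint group, time and group × time model does not suit it

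*Protocol article*

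**What the plan says.** The Academic performance section (Secondary outcomes) says: "Academic performance will be evaluated by utilising the school's end-of-term academic examinations, which comprehensively assess all the subjects". It names mathematics, language and an overall composite, and it gives the purpose as a comparison of arms: "a composite score for all subjects will be utilised to discern variations in academic performance between the intervention and control groups". It adds that "academic performance will not be assessed at the follow-up stage".

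Table 5 gives the timing as "By the end of term 1 and T2". Table 1 places the two assessments at 22–26 January (school term 1) and 1–4 July (the end of term 2).

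The Statistical analyses section sets one linear mixed model for the outcome variables, with group, "timepoints (pre-, post-intervention and follow-up) and group × time interactions". It also says: "Statistical analyses will be adjusted for the clustering effects at class level". It does not specify the random-effects structure, makes no exception for academic performance and mentions no rescaling of marks.

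**The concern.** A time term and a group × time term compare a later value with an earlier one on the same scale. For the shuttle run, the article takes care to keep test conditions constant across timepoints. For academic performance the instrument itself changes, because the January and July papers are different examinations.

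Two things follow. The time effect mixes change in attainment with change of paper. And if the two papers spread pupils differently, a baseline gap between the arms that arose by chance is stretched or shrunk, and the model reads this as group × time. With few classes per arm, such a gap is likely. Randomisation is stratified by PE teacher, which does nothing directly to balance academic standing. Academic performance is named in the abstract and in aim 1, and the Discussion presents it as a research gap, so the result will be read.

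**Working it through.** The article gives no numerical target or variance for academic performance, so there is no plan figure to reproduce here.

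**Inputs from the article.** One school, 8 classes and about 50 pupils per class (Sample size estimation). Four intervention classes: the Focus groups section takes 2 peer-coaches and 2 other pupils per intervention class, 16 in all, and 16/4 = 4. That leaves 4 control classes.

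**Assumed inputs (not in the article).** Class ICC for marks 0.05–0.20; ratio k of term 2 to term 1 mark SD 0.7–1.5; both arms sit the same papers.

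**Step 1: algebra.** Let s be a pupil's standing in term 1 SD units. With no treatment effect and unchanged standing, the term 1 mark is μ₁ + s and the term 2 mark is μ₂ + k·s.
- The time effect contains μ₂ − μ₁, the difference between papers. If the second paper is 10 marks harder and attainment is unchanged, the time effect is −10.
- In group × time, μ₂ − μ₁ cancels between arms. What remains is (k − 1) × D, where D is the baseline arm difference.

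**Step 2: size of a chance D.** SD(D) = √[2 × (ICC + (1 − ICC)/50)/4].
- ICC 0.05: √(2 × 0.069/4) = 0.186
- ICC 0.10: √(2 × 0.118/4) = 0.243
- ICC 0.20: √(2 × 0.216/4) = 0.329

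The 95% ranges (1.96 × SD) are about ±0.36, ±0.48 and ±0.64. With 40 pupils per class (20% dropout) the SDs hardly move: 0.192, 0.247 and 0.332.

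**Step 3: SD of the spurious term, |k − 1| × SD(D), in term 1 SD units.**

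| k | ICC 0.05 | ICC 0.10 | ICC 0.20 |
|---|---|---|---|
| 0.7 | 0.056 | 0.073 | 0.099 |
| 0.9 or 1.1 | 0.019 | 0.024 | 0.033 |
| 1.0 | 0 | 0 | 0 |
| 1.25 | 0.046 | 0.061 | 0.082 |
| 1.5 | 0.093 | 0.121 | 0.164 |

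For one trial with D = 0.2, the term is −0.06 at k = 0.7, +0.05 at k = 1.25 and +0.10 at k = 1.5.

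**Step 4: simulation with no treatment effect.** It used 3,000 runs, 8 classes of 50, a mark SD of 15, score reliability 0.8 and a second paper 10 marks harder; all mark properties are assumed. The mean interaction was about 0 in every setting. Rejection at the 5% level was:

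| | ICC 0.01 | ICC 0.05 | ICC 0.15 |
|---|---|---|---|
| Individual-level test of change, k = 1 | 4.9% | 4.6% | 4.8% |
| Individual-level test, k = 0.7 | 6.1% | 12.4% | 23.8% |
| Individual-level test, k = 1.4 | 5.8% | 12.0% | 22.9% |
| Class-level test of change, k = 1.4 | 5.1% | 5.4% | 4.8% |
| Individual-level test, k = 1.4, marks standardised within examination | 5.6% | 4.4% | 5.1% |

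The individual-level test is comparable to a model with participant and class random intercepts but no class × time effect.

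**Step 5: precision.** At k = 1.4 the SD of the interaction estimate was 1.32, 1.60 and 2.07 marks at ICC 0.01, 0.05 and 0.15, against 0.95, 0.94 and 0.96 after standardising. Part of that gap is only the larger unit of the second paper. Dividing the raw figures by 1.4 gives 0.94, 1.14 and 1.48. On a like-for-like basis, precision is therefore lost at ICC 0.05 and 0.15 but not at 0.01.

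**The case against.** The strongest reply is that a condensed article need not say how one secondary outcome is scored. The article never says that raw marks will be modelled, and it leaves the composite undefined; a fuller plan may contain the scaling. That stands, so silence on standardisation is not itself the point. The point is that the model the article does state does not fit the measure it does state.

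The reply has more that stands. The purpose given for this outcome is the comparison of arms, not change over time. All classes come from one school, so both arms presumably sit the same papers and a difference in difficulty drops out. The size of any distortion rests on an ICC and a spread ratio that the documents do not give, and it vanishes as k approaches 1. The excess type I error needs a model without class × time. The article promises class-level adjustment without fixing its form, so it neither commits to that model nor rules it out.

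A reader might infer that the group × time estimate is biased. It is not, on average over randomisations: the distortion depends on the imbalance that one trial happens to draw, and it can go either way. A reader might also infer that the model's equal-variance assumption fails. The documents do not support that: the spreads are unknown, checks of homogeneity of variances are planned, and the covariance structure is left open.

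**Conclusion.** The point holds as a minor to moderate one, confined to one secondary outcome; the primary outcome is untouched. Two parts rest on the article alone: the general model names three timepoints where this outcome has two, and its time effect is confounded with the change of paper. The effect on the arm comparison is conditional. It needs both a change in mark spread and a chance baseline difference. Under the assumed ranges its SD runs from 0 to about 0.16 term 1 SD. The inflated rejection rates (about 12% at ICC 0.05 and 23–24% at ICC 0.15, for k = 0.7 or 1.4) apply only to an analysis that ignores class × time variation.

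**What to change.** Give academic performance its own analysis statement:

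- Convert each mark to a z-score within examination and subject, with both arms pooled. Use the year-group mean and SD if the school can supply them, otherwise those of all trial pupils.
- Build the composite from these z-scores, so that no subject's weight depends on the spread of its paper.
- Estimate the arm difference in the term 2 score adjusted for the term 1 score, with class clustering. This adjustment already absorbs most of a linear change of scale for a single subject; the z-scores matter chiefly for the composite and for a common unit.
- If a change-type mixed model is kept instead, use two timepoints and include a class × time random effect.
- Do not interpret a time effect for this outcome.

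The simulation tested standardisation within examination alone, not the full adjusted analysis. The cost is a change of wording: the marks are already to be collected, and no new data are needed unless year-group figures are requested. The downside is that results are in SD units rather than marks.
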